# Relating therapy for voices (the R2V study): study protocol for a pilot randomized controlled trial

**DOI:** 10.1186/1745-6215-15-325

**Published:** 2014-08-16

**Keywords:** Auditory hallucinations, Voices, Interpersonal, Relationship, CBT, Psychosis

## Abstract

**Background:**

Evidence exists for the effectiveness of cognitive behaviour therapy for psychosis with moderate effect sizes, but the evidence for cognitive behaviour therapy specifically for distressing voices is less convincing. An alternative symptom-based approach may be warranted and a body of literature has explored distressing voices from an interpersonal perspective. This literature has informed the development of relating therapy and findings from a case series suggested that this intervention was acceptable to hearers and therapists.

**Methods/Design:**

An external pilot randomized controlled trial (RCT) comparing outcomes for 15 patients receiving 16 hours (weekly sessions of one hour) of relating therapy and their usual treatment with 15 patients receiving only their usual treatment. Participants will be assessed using questionnaires at baseline, 16 weeks (post-intervention), and 36 weeks (follow-up).

**Discussion:**

Expected outcomes will include a refined study protocol and an estimate of the effect size to inform the sample size of a definitive RCT. If evidence from a fully powered RCT suggests that relating therapy is effective, the therapy will extend the range of evidence-based psychological therapies available to people who hear distressing voices.

**Trial registration:**

Current Controlled Trials ISRCTN registration number 44114663. Registered on 13 June 2013.

## Background

The experience of hearing voices (verbal ‘auditory hallucinations’) is one of the prominent features of schizophrenia in current systems of diagnostic classification [1]. Voice hearing is reported to occur in approximately 70% of patients with this diagnosis [2], although the experience is also common in other mental health conditions such as post-traumatic stress disorder and borderline personality disorder [3]. National Institute for Health and Care Excellence (NICE) guidance in the UK recommends that psychological therapy in the form of cognitive behavioral therapy (CBT) should be offered to all patients who have a diagnosis of schizophrenia [4]. Although this is appropriate in the case of psychosis more broadly, where an evidence base exists for moderate effects [5], the impact of CBT for psychosis specifically on distressing voices is less convincing [6]. Therefore, consistent with a symptom-based approach [7], a voice-specific approach may be warranted. A recent review [6] was conducted of 16 published randomized controlled trials (RCTs) of CBT for psychosis that have reported at least one psychometrically validated outcome measure specifically related to voice hearing. The review found that the majority of studies failed to show a significant effect of CBT on voice hearing, and most of those that reported significant effects did so in the context of methodological weaknesses. Only one study reported an effect using a robust methodology. Interestingly, this was the only study that focused exclusively on voice hearing [8]. A factor that may have limited the effect of CBT upon voice hearing concerns outcome measurement - early trials used measures of voice frequency and severity, despite CBT not focusing upon the eradication of voices. The authors conclude by calling for more robustly designed RCTs of CBT aimed specifically at distressing voices. They draw attention to the potential for the integration of other psychotherapeutic techniques that have shown early promise for assisting voice hearers. In particular, the approach of trying to understand and adapt the interpersonal-like relationships that can develop with voices (see [9, 10] for a review).

There is an evolving body of literature that has explored the experience of hearing voices from an interpersonal perspective, examining the interaction that can occur between the hearer and the voice(s) that is heard. Findings suggest that hearers, regardless of diagnosis, can have integrated, personally coherent relationships with their voices [11]. Two studies using social rank theory found marked differentials of power and social rank between the hearer and the voice, which place the voice in a dominant position, and mirror perceptions of self in relation to significant social others [12, 13]. However, whilst there has been a focus on dominance, research has paid less attention to the role of intimacy and closeness within relationships with voices. If relationships with voices do mirror relationships in the social world, they are likely to be imbued with all the complexity and idiosyncrasy of social relationships. Relating theory [14] proposes that relating occurs on two axes: a vertical ‘power’ axis characterized at each polar end by ‘upper’ and ‘lower’ (analogous to power differentials), and a horizontal ‘proximity’ axis characterized at each polar end by ‘close’ and ‘distant’. Studies that have explored voice hearing experiences through the lens of relating theory report that distressing voices are perceived as relating dominantly and intrusively [15–17], and are responded to through distant relating from the hearer. Mirroring has also been found between proximity styles of relating to voices and those of the hearers within their social relationships [18].

Collectively, this body of research suggests that voices can be understood within interpersonal frameworks. This conceptualization has given rise to a new generation of therapeutic approaches that seek to modify the hearer-voice relationship. A pilot RCT [8] that looked at a therapeutic approach to address the power dynamic with voices that issue commands (cognitive therapy for command hallucinations [CTCH]) found significant reductions in compliance behaviour within the therapy group, and this finding has been replicated in a definitive trial [19]. A therapeutic focus upon closeness and intimacy has been developed by [name] *et al*. [16] in the form of relating therapy (RT) which aims to re-balance the hearer-voice relationship with regard to both power and proximity. Findings from a case series suggested that RT was acceptable to hearers who experienced persistent and distressing voices [16, 20]. Consistent with the call for evaluations of effectiveness to be methodologically rigorous [6], RT should now be evaluated within an RCT design.

### Research objectives and hypotheses

The main objective of the study will be to inform the development of a phase III definitive trial [21]. Specifically, this external pilot RCT will establish recruitment, retention, and follow-up rates to the trial, assess levels of adherence with the treatment, and establish treatment effect size relative to treatment-as-usual. This information will be used to finalize the design of the therapy protocol and the study protocol for the phase III trial.

This external pilot RCT is, by definition, underpowered to detect statistically significant effects. Voice-related distress, rather than voice activity (such as loudness or frequency) or voice attributions (such as beliefs about the origin of voices), is the primary target of the therapy. Therefore, the primary hypothesis for the definitive trial is that RT added to treatment-as-usual will reduce the distress associated with voice hearing compared with treatment-as-usual on its own.

Secondary hypotheses for the definitive trial are that RT will lead to: 1) Reductions in voice-related distress relative to the control condition that will be maintained over at least three months; 2) Reductions in voice-related distress that will be mediated by improvements in relating to and/or by voices (improvements in relating defined as reductions in voice dominance and intrusiveness, and hearer distance - measured by the Voice and You [VAY]questionnaire); 3) Improvements in recovery (measured by the Choice of outcome in CBT for psychoses [CHOICE] questionnaire), relating to people in the social world (measured by the shorter version of the Persons Relating to Others Questionnaire [PROQ3]), and mood and anxiety (measured by the Hospital Anxiety and Depression Scale [HADS]); and 4) Improvements in relating to people in the social world will be associated with improvements in relating to and/or by voices (improvements in relating defined as reductions in voice dominance and intrusiveness, and hearer distance - measured by the Voice and You [VAY] questionnaire).

## Methods/Design

An external pilot RCT will compare the outcomes for patients receiving the RT intervention (in addition to their usual treatment) to outcomes for patients receiving only their usual treatment. Participants who consent will be randomized to either RT (plus treatment-as-usual) or to treatment-as-usual (TAU) only (see Figure 1). Randomization will be conducted by a statistician independent to the research team. Outcomes will be assessed at baseline (pre-randomization - Time 0), 16 weeks (post-intervention - Time 1), and 36 weeks (follow-up - Time 2). Time 1 and 2 assessments will be conducted blind by a researcher independent of the therapy process. Adherence to the therapy protocol will be assessed by an independent rater assessing a random selection of early, middle, and late recorded sessions using a modified version of the cognitive therapy checklist [22].

**Figure 1 Fig1:**
[figure not shown]
**Flow diagram for R2V trial.**

### Participants

The study aims to recruit approximately 30 patients from an NHS mental health trust in the south of the UK. Allowing for attrition from the study, there will be at least 12 completer participants per condition, in line with recommendations for pilot RCTs [22]. Inclusion criteria require that participants have been hearing distressing voices for at least one year, irrespective of diagnosis, and score 3 or above on either the intensity of distress item or the amount of distress item on the Psychotic Symptoms Rating Scale - Auditory Hallucinations Scale (PSYRATS-AHRS) [23] at the time of consent. People will be excluded on the grounds of organic illness, a primary diagnosis of substance misuse, or are currently receiving psychological therapy for distressing voices. Each participant will give informed consent before entering the trial.

### Planned intervention

The intervention will consist of a maximum of 16 hours (weekly sessions of one hour) of individual RT. The therapy protocol consists of three phases:

Phase 1: socialization to RT and its implications for the interrelating between hearer and voice. Use of chapter 3 from *Overcoming Distressing Voices*
[24] to guide discussions about relationships in terms of power and proximity, and linking this discussion to participant’s experiences of relating to people and distressing voices. Consideration of the typical ways of responding to negative relating (giving in, fighting back, and trying to escape). Introduction of the possibility of relating differently to voices.

Phase 2: exploration of themes within the relational history of the hearer and their experience of relationships with voices, and interpersonal relating within the family and social environment (identifying any prominent themes, such as abuse, disempowerment, or rivalry). Development of connections across all forms of relating. If appropriate and desired, generating formulation(s) that link past and present forms of relating.

Phase 3: exploration and development of assertive approaches to relating (to the voice and socially). Selection of a relationship to be the focus of intervention. Use of chapter 7 from *Overcoming Distressing Voices*
[24] to explore current utterances of chosen voice or person, responses to these utterances, identifying responses as passive, aggressive, or assertive and generation of assertive responses to chosen voice or other. Experiential role plays are a critical part of Phase 3 and are used to explore the motives of the voice (and other people) and to practice relating in an assertive manner.

The intervention will be offered by five therapists. Two of the therapists (including the first author) are familiar with the therapy, having previously delivered it within the case series [16, 20]. The three remaining therapists are experienced in the delivery of psychological therapy for psychotic experiences within trials, and will receive training from the first author.

### Treatment-as-usual

All participants will be receiving treatment-as-usual from an NHS mental health service. This will include anti-psychotic medication and regular contact with a member of their clinical team. Participants will be required to have no definite plan to receive psychological therapy for voices at the time of consenting to the study. There are no other requirements for previous or future therapy.

### Measures

#### Primary measure

Psychotic Symptoms Rating Scale (PSYRATS-AHRS) - an 11-item rating scale designed to measure the severity of different dimensions of the voice hearing experience [23]. Items include frequency, duration, loudness, intensity of distress, and controllability and are grouped together in four factors [25]; distress (negative content, distress, and control), frequency (frequency, duration, and disruption), attribution (location and origin of voices), and loudness (loudness item only). The authors report excellent psychometric properties [23].

#### Secondary measures

Choice of outcome in CBT for psychoses (CHOICE) – CHOICE is a 21-item self-report questionnaire developed with service users to assess goals for CBT for psychosis that are relevant to recovery, including self confidence, ways of dealing with unpleasant feelings and emotions, positive ways of relating to people, knowing they are not the only person who has unusual experiences, and a positive purpose and direction in life [26]. CHOICE has been found to be reliable and valid.

Voice and You (VAY) - the VAY is a 28-item measure of interrelating between the hearer and their predominant voice [15]. Relating is measured across four scales: two concerning the hearer’s perception of the relating of the voice (voice dominance and voice intrusiveness), and two concerning the relating of the hearer (hearer distance and hearer dependence). The VAY has good internal consistency (α >0.80 for all scales) and acceptable test-retest reliability (r >0.7 for all scales).

The Shorter version of the Persons Relating to Others Questionnaire (PROQ3) - the PROQ3 is a 40-item questionnaire that assesses relating across eight scales which correspond to the relating positions within Birtchnell’s Interpersonal Octagon [27]. The PROQ3 has acceptable internal consistency (α >0.70 for all scales) and its eight-factor structure is supported by factor analysis and multidimensional scaling analysis.

Hospital anxiety and depression scale (HADS) - the HADS is a 16-item measure of symptoms of anxiety and depression that has well-established psychometric properties [28].

### Analysis

The aim of this pilot study is to establish: 1) Recruitment, retention, and follow-up rates to the trial. This will be recorded as: (a) the number of research assistant hours required to obtain consent for one participant, (b) the percentage of participants who complete the Time 1 assessment, and (c) the percentage of participants who complete the Time 2 assessment; 2) Level of adherence with the treatment. This will be recorded as the percentage of participants who complete at least eight RT sessions (50% of the maximum of 16 sessions); 3) Treatment effect size relative to treatment-as-usual. A mixed one way analysis of variance (ANOVA) with post-hoc tests, where appropriate, will be conducted in order to calculate the group (two levels: RT + TAU or TAU) by time (three levels: T0, T1 and T2), interaction effect size, and its 95% confidence interval on the PSYRATS-AHRS; 4) Minimally clinically important difference. Taking a reduction of 1.0 on a PSYRATS-AHRS item as having clinical meaning, a difference of 5 in change scores (T0-T1 and T0-T2) between the two groups for the 5-item distress subscale will represent a minimally clinically important difference and be contained within the 95% confidence interval for the effect size.

This information will be used to refine the therapy protocol and to design the definitive trial. The group by time effect size on the PSYRATS-AHRS will be used for the power calculation for the definitive trial whilst taking into account the minimum clinically important difference on the PSYRATS-AHRS.

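### The group-by-time ANOVA treats baseline as an outcome; a mixed model with baseline as covariate and all available follow-up scores would usually give a more precise estimate

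*Protocol article*

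**What the plan says.** The Analysis section of the protocol article fixes the method: "A mixed one way analysis of variance (ANOVA) with post-hoc tests, where appropriate, will be conducted". Its output is the group "by time (three levels: T0, T1 and T2), interaction effect size, and its 95% confidence interval on the PSYRATS-AHRS". T0, measured before randomisation, is therefore a level of the within-person factor. The section then says that this effect size will be used to power the definitive trial, taking account of a minimally important difference defined as "a difference of 5 in change scores (T0-T1 and T0-T2) between the two groups for the 5-item distress subscale".

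On numbers, the Abstract describes a trial "comparing outcomes for 15 patients receiving 16 hours (weekly sessions of one hour) of relating therapy" against 15 on usual treatment, and the Participants section adds: "Allowing for attrition from the study, there will be at least 12 completer participants per condition". The Analysis section counts completion of T1 and of T2 separately, so partial follow-up is foreseen. The article does not say who enters the ANOVA or how a missing assessment is treated.

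**The concern.** A score taken before randomisation cannot be affected by treatment. It is most useful as a covariate. Placed in the time factor, it is simply subtracted, which amounts to fixing the regression slope of follow-up on baseline at 1. Unless the true slope is close to 1, this adds noise. It also leaves a chance baseline difference between small arms only partly dealt with, because patients who start high tend to fall back in either arm. The entry threshold on a distress item of the same scale makes such regression to the mean likely.

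A classical mixed ANOVA also needs all three scores per person. Without imputation, one missed visit removes the other follow-up score too.

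Finally, the interaction over three times and two groups has (3 - 1) x (2 - 1) = 2 degrees of freedom. A single effect size for it is not a difference in points at T1 or at T2, and that is what the 5-point benchmark requires.

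What is at stake is the precision and robustness of the estimate that will size the next trial.

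**Working it through.** **Plan's own figure.** There is no power-based sample size to reproduce. Fifteen per arm with at least 12 completing implies a loss of up to 3/15 = 20%. Conversely 12/0.80 = 15 per arm, or 30 in total, which agrees with the stated target. The 20% is back-calculated, not stated.

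**Assumed inputs.** The documents give no SD and no correlation rho between baseline and follow-up. I take equal SDs and rho from 0.3 to 0.9.

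**Variance of one contrast, in SD-squared units per person**
- Change score: 2(1 - rho)
- Baseline-adjusted: 1 - rho^2
- Ratio: (1 + rho)/2
- Estimating the slope costs a factor 1 + 1/(N - 4): 1 + 1/20 = 1.050 at N = 24, and 1 + 1/26 = 1.038 at N = 30.

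| rho | Ratio | Ratio x 1.050 (N = 24) |
|---|---|---|
| 0.3 | 0.65 | 0.68 |
| 0.5 | 0.75 | 0.79 |
| 0.7 | 0.85 | 0.89 |
| 0.9 | 0.95 | 1.00 |

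With unequal SDs s0 (baseline) and s1 (follow-up), the change-score variance exceeds the adjusted variance by (s0 - rho s1)^2. This is never negative. If the entry threshold narrows s0 below s1, the gain shrinks, and it reaches zero when s0 = rho s1.

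**Standard error of the group difference at rho = 0.5, in SD units**
- Change, 12 per arm: sqrt(2/12 x 1.00) = 0.408
- Adjusted, the same 12 per arm: sqrt(2/12 x 0.75 x 1.050) = 0.362
- Adjusted, all 15 per arm seen at that visit: sqrt(2/15 x 0.75 x 1.038) = 0.322

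The last figure is the best case for a visit: everyone attends it, and the losses under listwise deletion come only from the other visit.

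**Chance imbalance.** With 15 per arm the baseline difference has SD sqrt(2/15) = 0.37. It shifts the change contrast by (1 - rho) times itself, about 0.18 SD at rho = 0.5 for a difference of that size. Over repeated randomisations the shift averages to zero.

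**Simulation** (15 per arm, effect 0.5 SD, about 20% loss, 6,000 to 8,000 runs, all assumed)
- *T1 missing completely at random, rho = 0.5.* SD of the T2 estimate: 0.412 for the complete-case change contrast, 0.320 for the adjusted estimate using all T2 scores.
- *T2 missing completely at random, rho = 0.5.* 0.410 for change, and 0.366 both for adjusted complete cases and for the likelihood model that also uses T1. Here the gain comes from the covariate, not from the extra T1 scores.
- *No missing data, or missing completely at random.* Neither method is biased beyond simulation error.
- *RT dropout depending on baseline score.* The complete-case change contrast was off by 0.10 to 0.14 SD, understating the benefit; the adjusted model was off by about 0.
- *RT dropout depending on T1 score.* Change was off by 0.00 to 0.06 SD, according to the correlations; the model by about 0.

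**Reach into the next trial (illustrative).** For an effect of 0.5 SD, 80% power and two-sided 5%, the number per arm with change scores versus adjustment is 88 v 58 at rho 0.3, 63 v 48 at 0.5, 38 v 33 at 0.7 and 13 v 12 at 0.9. This applies only if the definitive trial carries the same analysis forward.

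**The case against.** The strongest reply is that much of the damage depends on things the article does not state, and most of that reply stands.

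- A reader might infer that the plan drops anyone with a missed visit. It does not say so. The mention of completers is a recruitment allowance, not an analysis set, and missing-data handling may be in a full protocol or analysis plan not shown. Deletion is only the usual behaviour of the named method.
- A reader might infer that the ANOVA ignores baseline or is biased. It subtracts baseline, and over randomisations the change contrast is unbiased. Change scores are named only in defining the important difference; that the ANOVA contrasts are changes from T0 follows from the three-level time factor.
- A reader might infer that a mixed model cures attrition and uses all 30 patients. With T0 as covariate, a patient with no follow-up score adds nothing to the contrast. If patients who gain nothing leave before T1, the new model misses them just as the ANOVA does. If dropout depends on unseen outcomes, neither method is protected.
- A reader might take T1 as the primary time point and a lost T1 score as the main harm. The article names no primary time point and lists both changes equally.
- A reader might object to sphericity over gaps of 16 and 20 weeks. Time is categorical here, so unequal gaps do not in themselves violate it, and standard corrections exist.
- The trial is described under Research objectives and hypotheses as underpowered by definition, so no confirmatory claim rests on the choice. The power calculation will also weigh the important difference.

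None of this removes the core. The method and the role of T0 are stated choices, and the estimate with its CI is a main product of the pilot.

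**Conclusion.** The concern holds in limited form. The named analysis uses a pre-randomisation score as an outcome and so usually gives a less precise estimate than adjusting for it. At 24 completers the adjusted variance is about 0.68 to 0.89 of the change-score variance for rho 0.3 to 0.7, with no gain near 0.9. These ratios assume equal SDs, and neither SDs nor rho are in the documents.

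A further gain from keeping scores of partly followed patients arises only if the ANOVA would in fact be run on complete cases. Protection from bias extends only to dropout that depends on observed data. Severity is low to moderate: the effect is on the quality of an estimate that informs the next trial's size, not on a confirmatory test.

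**What to change.** Replace the ANOVA with a linear mixed model for PSYRATS-AHRS scores at T1 and T2, with T0 score as covariate, group, time, group-by-time, unstructured covariance and a small-sample degrees-of-freedom correction. Include every randomised participant with at least one follow-up score, analysed as allocated, and say so. Report the adjusted difference with 95% CI at T1 and at T2. Fit the same model to the distress subscale, so that the 5-point benchmark can be read against a difference in points at each visit; this leaves the plan's choice of measures unchanged. Report how many participants have no follow-up score, since the model cannot recover them.

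The cost is a change of analysis wording, one degree of freedom (1/26 to 1/20, about 4-5% of variance) and an explicit missing-at-random assumption. T0 is already collected. The ANOVA can be kept as a sensitivity analysis if wanted.

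### The 5-point clinical difference is to lie inside the confidence interval of an effect size on a different scale and contrast, and containment is a poor reading of clinical importance

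*Protocol article*

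**What the plan says.** The Analysis section lists four aims; the third and fourth matter here.

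- **Effect size (third aim).** A mixed ANOVA is to give the group (two levels) by time (three levels) "interaction effect size, and its 95% confidence interval on the PSYRATS-AHRS". The Primary measure section describes the PSYRATS-AHRS as "an 11-item rating scale designed to measure the severity of different dimensions of the voice hearing experience", with distress as one of four factors. The metric of the effect size is not given.
- **Minimally clinically important difference, MCID (fourth aim).** The starting point is "Taking a reduction of 1.0 on a PSYRATS-AHRS item as having clinical meaning". This becomes "a difference of 5 in change scores (T0-T1 and T0-T2) between the two groups for the 5-item distress subscale", which "will represent a minimally clinically important difference and be contained within the 95% confidence interval for the effect size".

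The section closes by saying that the interaction effect size will drive the definitive trial's power calculation, with the MCID taken into account. There the MCID is attributed to the PSYRATS-AHRS, without mention of the subscale.

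**The concern.** There are two difficulties. First, the 5 and the interval that should contain it are not the same kind of quantity. The 5 is a raw difference in change on five items, over two separate intervals. The interval belongs to a three-time-point interaction on the PSYRATS-AHRS.

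Second, even if the units are aligned, containment looks in both directions around 5. It treats an interval wholly above the MCID like one wholly below it, and it can be satisfied because the interval is wide.

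This is the plan's only statement that sets the estimated treatment effect against clinical importance, and the Analysis section carries both the effect size and the MCID into the design of the definitive trial. A misread pilot interval could therefore distort that trial's target difference.

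**Working it through.** **Inputs from the protocol.** One point per item; five items; 95% confidence; 15 randomised per arm (Abstract, Methods/Design) and at least 12 completers per arm (Participants). **Assumed:** the SD of change on the distress subscale, which is not given; I use 3 to 8 points. Positive differences favour relating therapy.

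**The plan's own figure.** 5 items × 1.0 point = 5 points. This reproduces.

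**Step 1: can the stated interval contain 5?** Three readings of the unstated metric:

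- *Proportion of variance (eta-squared type).* It cannot exceed 1, so its interval can never contain 5.
- *Standardised mean difference d.* With SE = √(2/n + d²/(4n)), at n = 12 and d = 1: SE = √(0.1667 + 0.0208) = 0.433, and the interval is 1 ± 1.96 × 0.433 = 0.15 to 1.85. The upper limit reaches 5 only when the observed d is about 3.7 (n = 12) or 3.8 (n = 15).
- *Raw difference.* Here 5 can lie inside. However, the effect size is placed on the PSYRATS-AHRS while the 5 belongs to the subscale, and a two-degree-of-freedom interaction is not the same as two separate change contrasts.

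**Step 2: suppose the interval is in raw subscale points.** For one change contrast, half-width = t(0.975, 2n−2) × SD × √(2/n). At n = 12 and SD 5: 2.074 × 5 × 0.408 = 4.23.

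The interval contains 5 exactly when a two-sided 5% t-test of the hypothesis that the difference equals 5 does not reject. The probability follows from the noncentral t distribution with noncentrality (true difference − 5)/(SD × √(2/n)). At true difference 0 and SD 5 this is −5/2.041 = −2.45. It agrees with simulation of 200,000 trials per scenario.

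Probability that the 95% interval contains 5, with 12 per arm:

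| Assumed SD | Half-width | True 0 | True 2.5 | True 5 | True 10 |
|---|---|---|---|---|---|
| 3 | 2.54 | 3% | 50% | 95% | 3% |
| 4 | 3.39 | 17% | 69% | 95% | 17% |
| 5 | 4.23 | 35% | 78% | 95% | 35% |
| 6 | 5.08 | 50% | 84% | 95% | 50% |
| 8 | 6.77 | 69% | 89% | 95% | 69% |

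- *From above.* At SD 5 and a true difference of 10, the interval lies wholly above 5, so containment is not met, in 65% of trials. The observed difference must exceed 5 + 4.23 = 9.23 for this (taking the sample SD as 5).
- *From imprecision.* At a true difference of 0 the frequency rises with the SD. At SD 5 it falls from 35% with 12 per arm to 25% with 15 per arm, so better retention makes the condition harder to meet.

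**Step 3: would a one-sided version do?** Suppose only the upper limit had to reach 5. At SD 5, 12 per arm and no true effect, this is still met in about 35% of trials. It removes the problem from above but not the one from imprecision. If the interval must also exclude 0, the figure falls to about 2.5%, because in 32.6 of those 35.1 percentage points the interval contains both 0 and 5.

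**The case against.** The strongest reply is that no rule is being applied. A reader might infer that a therapy passes or fails on this sentence. The protocol does not support that: it attaches no stop, go/no-go or efficacy claim, it declares the pilot underpowered, and it uses the results to refine the therapy and design the next trial. The sentence can be read as a loose plausibility statement, and a sensible designer would not treat an interval wholly above 5 as bad news. This stands, and it lowers the severity.

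A reader might also infer that the effect size is standardised, so that 5 is flatly impossible. The text does not say standardised, and a raw contrast is a possible reading. What stands is that metric, scale and contrast are not stated consistently; the impossibility holds only for a variance-explained effect size.

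The equality at true differences of 0 and 10 is symmetry about 5, and at exactly 5 the frequency is 95% at any precision. The SDs are assumed, so the percentages are illustrations. Symmetry is nevertheless the fault: no effect and twice the MCID should not look alike.

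Finally, naming both change intervals is not itself an error. The research objectives put distress reduction first and its maintenance second, which already suggests an order.

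**Conclusion.** The statement is wrong as written and should be fixed, at moderate rather than high severity. The mismatch of scale and contrast follows from the text and needs no assumption. The weakness of containment follows from its two-sided form. Its size depends on the unknown SD: with 12 per arm and SD 4 to 6, it is met in about 17% to 50% of trials with no true effect and equally often at twice the MCID. These figures also assume normally distributed change scores with equal variances and a simple two-group comparison of change. The consequence is a misleading input to the definitive trial's design. It is not a false efficacy claim, because the pilot makes none.

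**What to change.** Keep the planned mixed ANOVA. Add the between-group difference in change on the 5-item distress subscale, in raw points, for T0-T1 and for T0-T2, each with its 95% confidence interval. Name the metric of the interaction effect size, and say that the MCID of 5 refers to the subscale wherever it appears.

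Replace the containment condition with a statement of where each interval lies relative to both 0 and 5:

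- wholly above 5: benefit beyond the MCID;
- reaching 5 and excluding 0: a benefit, possibly an important one;
- including both 0 and 5: inconclusive;
- wholly below 5: an important benefit is unlikely.

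Do not use the upper limit reaching 5 as a criterion by itself, for the reason in Step 3 of the working.

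The cost is a few sentences and a small amount of extra reporting; no new data and no larger sample are needed. The downside is that the result may often be inconclusive at this size. With 12 per arm and SD 5, the interval includes both 0 and 5 in about 33% of trials at a true difference of 0 or 5, and in 57% at 2.5. That is a fair description of what the pilot can show.
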